## Abstract

**Background:**

*Lactobacillus coryniformis* K8 CECT5711 has immune-modulating properties, enhances the immune response to viral antigens leading to the production of specific antibodies, and has anti-inflammatory activity, which may help to prevent uncontrolled inflammatory processes leading to respiratory and other organ failures.

**Objective:**

The purpose of this study is to evaluate the effect of the consumption of a probiotic strain on the incidence and severity of COVID-19 in health personnel who carry out their professional work among patients with infection or suspected infection by SARS-CoV-2.

**Methods:**

This is a double-blind randomized clinical trial in which the experimental group will receive a capsule of *L coryniformis* K8 per day (3×10^9^ colony former units/day), and the control group will receive a daily placebo capsule consisting of maltodextrin. A sample size of 314 volunteers was calculated. Volunteers must meet the following inclusion criteria: older than 20 years and active health personnel caring for patients with COVID-19, including all professionals such as medical doctors, nurses, and caretakers at the 2 referral hospitals that treat patients with COVID-19. The main outcome of the clinical trial will be the incidence of symptomatic infection by SARS-CoV-2 in personnel who care for patients with suspected or confirmed COVID-19.

**Results:**

The study had to be extended to the 2 referral hospitals that treat patients with COVID-19 in the province of Granada (Andalusia, Spain); Hospital San Cecilio and Hospital Virgen de las Nieves. A total of 255 individuals met the inclusion criteria and were randomly assigned to one of the 2 groups.

**Conclusions:**

The results of this randomized controlled trial will provide valuable information regarding the administration of *L coryniformis* K8 against COVID-19, including whether there are fewer infectious processes due to this virus or, in case of occurrence, whether the disease is milder in participants taking the probiotic strain.

**Trial Registration:**

ClinicalTrials.gov NCT04366180; http://www.clinicaltrials.gov/ct2/show/NCT04366180

**International Registered Report Identifier (IRRID):**

RR1-10.2196/37857

## Introduction

Humans have consumed lactic bacteria throughout history, but it was at the beginning of the 20th century when this consumption was first related to beneficial properties for health [1]. From that moment on, multiple studies both in vitro and in vivo have shown the beneficial effects that the consumption of this type of bacteria, called probiotics, has on health. Effects such as the improvement of intestinal function [2,3], prevention of intestinal infections [4], and immunomodulation have been widely demonstrated [5]. In addition to these beneficial effects, the consumption of probiotics has been related to a reduction in the incidence and severity of respiratory infections [4,6].

Oral administration of lactic acid bacteria has been associated with an increase in innate and acquired immune responses [7,8]. The consumption of certain strains has been shown to induce an increase in IgA related to the anti-infective properties of probiotic bacteria in diarrhea [9,10]. Innate immunity is increased through an increase in the proportion and activity of phagocytic cells of the immune system, such as monocytes and neutrophils. The function of natural killer cells is also enhanced by the consumption of probiotic bacteria [11]. Activation of the innate immune system is essential, as it produces cytokines that will lead to more specialized activation of the specific immune response. It has been suggested that it is through this mechanism that probiotic bacteria activate the immune response, thus being able to function as adjuvants in vaccination processes [12].

The European Food Safety Agency (EFSA) has published guidelines on how studies should be conducted to demonstrate the effect of a probiotic or natural ingredient on the immune system. Among its recommendations is the use of vaccination protocols that demonstrate how the administration of the probiotic translates into an improvement in the response to an antigen [13]. Recently, a study carried out at the Center Institute of Food Science and Technology and Nutrition of the Spanish National Research Council demonstrated that the administration of *Lactobacillus coryniformis* K8 CECT5711 increases the response of specific antibodies against hepatitis A in a vaccination protocol against this virus [14]. In addition, a certain effect on memory T-helper lymphocytes was observed, which increased in the probiotic group with respect to baseline values (mean 660, SD 223 cells/µL vs mean 551, SD 213 cells/µL). These results highlight the potential of this probiotic strain to improve the immune response against viral antigens.

To evaluate this activity that boosts the immune response, another study was carried out in an older population. This population is more susceptible to infections due to the characteristic immunosenescence of age. A total of 98 older people residing in nursing homes participated in this study. The volunteers received a daily capsule of *L coryniformis* K8 CECT5711 (3×10^9^ colony former units/day) for 2 weeks prior to being vaccinated against the flu or a placebo. The percentage of seroconversion was higher in the group receiving the probiotic than in the control group (93.1% vs 72.7%; *P*=.04). During the months of October to April, the volunteers were monitored, and the incidence of local symptoms associated with respiratory infections (sore throat, cough, and nasal congestion) was 48% lower in the group that received the probiotic strain than in the control group (*P*=.007). Furthermore, the consumption of analgesics was significantly reduced in this group by 86% (*P*=.008) [15]. This latest study corroborates the strain’s ability to improve the immune response against viral antigens even in the older population.

We are currently experiencing a pandemic due to COVID-19 (the English acronym for COVID-19), which started in the Chinese city of Wuhan in December 2019. Having reached more than 100 territories, the disease was declared a pandemic by the World Health Organization on March 11, 2020 [16]. The number of confirmed cases continued to grow until reaching 5,371,660 cases worldwide on May 22, 2020. In Spain, at the end of May 2020, despite the containment measures initiated in early March, more than 235,772 cases were registered, and of these patients, more than 27,940 died [17].

The COVID-19 infection produces flu-like symptoms, including fever, dry cough, dyspnea, myalgia, and fatigue. In severe cases, it is characterized by pneumonia, acute respiratory distress syndrome, and septic shock, which lead to death in approximately 3% of those infected. Transmission occurs through small droplets that are emitted when speaking, sneezing, or coughing by a carrier and pass directly to another person through inhalation or by contact with contaminated objects in the recipient’s nasal and ocular mucous membranes. Symptoms start after approximately 7-20 days of exposure, and prevention at the population level consists of frequent hand washing, disinfecting surfaces with alcohol, and avoiding close contact with other people [15].

Some drugs have been proposed as antiviral treatments, such as hydroxychloroquine, lopinavir, ritonavir, and others; severe pneumonia is treated with broad-spectrum antibiotics. There is no up-to-date, effective treatment for the COVID-19 infection.

An article published in March 2020 shows how the immune response to the COVID-19 virus is similar to the response generated by the influenza virus [18]. Some authors propose the use of probiotics as a strategy to mitigate the effects of viruses [19].

Health care workers (HCWs) are at increased risk of COVID-19 infection due to close contact with highly infectious patients as well as exposure to undiagnosed or subclinical infected cases. The stress and physical exhaustion associated with the pandemic may also impact the immune response of HCWs [20]. A recent study examined 97 studies and found that approximately 11% of patients with COVID-19 were people with underlying disease [21]. This represented a considerable percentage of all COVID-19 cases [22]. Although the number of severe cases and mortality among HCWs was lower than in other populations [21], the number of COVID-19 cases has led to a shortage of HCWs, thus adding an extra burden to the fight against this pandemic.

It has been suggested by several authors that probiotics could play a role in preventing and alleviating the severity of COVID-19 due to their immune-modulating, anti-inflammatory, antioxidant, and antiviral properties [23-25]. The *Loigolactobacillus coryniformis* K8 CECT 5711 strain has been shown to have the immune-modulating capacity in adults [26] and children [27,28]. Research has shown that this strain causes an increase in hepatitis A virus antibody levels after oral administration in healthy adults as part of hepatitis A vaccination [14]. A study in older people found that the administration of *L coryniformis* K8 strengthened the immune response to influenza vaccination and reduced symptoms associated with respiratory infections [15]. A recent randomized controlled trial conducted with nursing home residents showed the benefits of *L coryniformis* K8 in the COVID-19 pandemic. This is because it may enhance the specific immune response following COVID-19 infection and also aid vaccine-specific responses among the older population [29].

In this context, it is proposed that the immunomodulatory properties of *L coryniformis* K8 CECT5711 might be useful for COVID-19 management.

## Methods

### Aim of the Study

The objective of this study is to evaluate the effects of the consumption of *L coryniformis* K8 on the incidence and severity of symptomatic infection by SARS-CoV-2 and the severity of COVID-19 in HCWs who carry out their professional work among patients with infection or suspected infection by SARS-CoV-2 at 2 referral hospitals that treat individuals with COVID-19 in the province of Granada (Andalusia, Spain).

### Description of Treatments

The administration of the experimental product and the placebo will be carried out in the form of a gelatin capsule that will have the same weight, consistency, and color.

The Experimental Group will receive hard gelatin capsules that will contain 3×10^9^ colony forming units of *L*
*coryniformis* K8 (120 mg), 10 mg magnesium stearate, and 120 mg maltodextrin.

The control group will receive hard gelatin capsules that will contain magnesium stearate (10 mg) and maltodextrin (220 mg). Individuals from both groups will take 1 capsule a day (preferably with dinner).

Capsules for the probiotic and placebo will be provided by Biosearch Life (Granada, Spain).

### Study Design

The study is a nutritional, randomized, double-blind, controlled, and parallel-group observational prospective cohort study. Volunteers will be distributed into 2 groups: a control group and an experimental group. The study will be performed as shown in Figure 1.

The trial has been registered on ClinicalTrials.gov (NCT04366180).

**Figure 1 figure1:**
[figure not shown]
Study flowchart.

### Ethics Approval

This clinical research protocol has been prepared with full understanding and in accordance with the standards of Good Clinical Practice in accordance with CPMP/ICH/135/95, the Declaration of Helsinki (64th General Assembly, Fortaleza, Brazil, October 2013), ISO 14155, and all relevant national guidelines. All investigators participating in the study are appropriately qualified. The protocol was approved by the Research Ethics Committee for the province of Granada (3/2020_P_054; CEIM/CEI Province of Granada). Volunteers will be included in the study after informed written consent is obtained.

### Participants, Intervention, and Outcomes

#### Inclusion Criteria

The inclusion criteria included individuals older than 18 years and active HCWs, including all professional categories such as medicine, nursing, and caretaking, who attend cases classified as positive or suspicious for COVID-19 in the emergency department, intensive care unit (ICU), or in the wards designated to care for such patients; and the ability to complete the surveys and having signed the informed consent.

#### Exclusion Criteria

The exclusion criteria excludes individuals with a positive test for COVID-19 confirmed by polymerase chain reaction or serology, individuals with concomitant pathology such as HIV, transplantation, active cancer, or other active immunosuppression, and women who are pregnant or intend to become pregnant in the subsequent months.

#### Recruitment

The recruitment of participants will take place at the San Cecilio University Clinical Hospital and at the Virgen de las Nieves University Hospital in Granada among HCWs with high exposure to patients with COVID-19.

#### Randomization, Allocation, and Blinding

Patients will be randomly allocated to a control group or experimental group in a 1:1 ratio by the block randomization method with a block size of 4. Participants and investigators will be blinded to the treatment allocation during the course of the intervention. The blind will be broken after statistical analysis is completed.

Capsules for the control and experimental groups will be provided in white containers labeled with a random number.

#### Intervention

Participants meeting the inclusion criteria will be randomly assigned to the control or experimental group. During the intervention, participants will be asked to ingest a capsule per day with some food (preferably with dinner). Follow-up visits will be scheduled at the beginning, midpoint (1 month), and end of the intervention period (2 months). At the first visit, baseline data (age, sex, lifestyle, medication, concomitant diseases, and current symptoms) will be collected. At follow-up visits, data about symptoms, medication, and adverse effects will be recorded (Table 1).

**Table 1 table1:** Detailed study procedures.

Visits (V) per week (W)	V1 (W0)	V2 (W4)	V3 (W8)	V4 (12 months)
Informed consent form	✓			
Inclusion or exclusion criteria	✓			
Randomization or allocation	✓			
Treatment distribution	✓			
Basal data	✓			
COVID-19 test	✓	✓^a^	✓	
Symptoms questionnaire		✓	✓	
Medication questionnaire	✓	✓	✓	
Adverse effects questionnaire		✓	✓	
Return of unconsumed capsules			✓	
Evaluation of the immune response to the vaccine				✓

^a^COVID-19 test data would be collected only if performed.

### Outcomes Measures

#### Primary Outcomes

The main outcome will be the incidence of symptomatic SARS-CoV-2 infection confirmed by polymerase chain reaction or serology in HCW caring for patients with suspected or confirmed COVID-19 at the San Cecilio Clinical University Hospital and at the Virgen de las Nieves University Hospital.

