### Sample Size

Given that the current rates of infection among health professionals worldwide are very different, the sample size has been based on the comparison of 2 independent proportions for the use of the chi-square test. For an α of 5% and a power of 80%, taking a percentage of affected individuals in the control group of 15% and 10% as the minimum meaningful difference to be detected, a sample of 157 per branch would be necessary, taking into account a loss of 10% of participants.

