## Discussion

### Principal Findings

This study is conducted to evaluate the efficacy of the effects of *L coryniformis* K8 consumption on the incidence and severity of COVID-19 in HCWs working with SARS-CoV-2–infected or suspected patients in referral hospitals for patients with COVID-19 in the province of Granada. This randomized controlled trial aims to study whether the consumption of *L coryniformis* K8 will reduce the incidence of SARS-CoV-2 infection in the staff caring for patients with suspected or confirmed COVID-19 disease at the San Cecilio University Hospital and Virgen de las Nieves University Hospital. For this purpose, the incidence of hospital admissions caused by SARS-CoV-2 infection, both in the general hospitalization area and in the ICU area, will be studied in HCWs caring for SARS-CoV-2–infected patients.

It is important to determine the prevalence of pneumonia caused by SARS-CoV-2 infection and the need for oxygen supply to these patients. The presence of fever will be studied, and the number of days will be quantified, as well as the persistence of cough and feeling of fatigue. On the other hand, it will also be assessed whether these workers have needed pharmacological treatment.

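### The primary outcome counts symptomatic infection, but the restated aim, abstract conclusion and hypothesis speak of fewer infections, and no listed outcome counts all confirmed infections

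*Protocol article*

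**What the plan says.** Three places in the protocol article make symptoms part of the event. Primary Outcomes reads "The main outcome will be the incidence of symptomatic SARS-CoV-2 infection confirmed by polymerase chain reaction or serology". The abstract's Methods paragraph reads "The main outcome of the clinical trial will be the incidence of symptomatic infection by SARS-CoV-2". Aim of the Study says the trial evaluates effects "on the incidence and severity of symptomatic infection by SARS-CoV-2 and the severity of COVID-19 in HCWs". The abstract's Objective names the disease rather than the infection: "evaluate the effect of the consumption of a probiotic strain on the incidence and severity of COVID-19 in health personnel".

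Three other places drop the condition:
- Discussion, Principal Findings, restates the aim as whether the product "will reduce the incidence of SARS-CoV-2 infection in the staff caring for patients with suspected or confirmed COVID-19 disease".
- The abstract's Conclusions say the results will show "whether there are fewer infectious processes due to this virus or, in case of occurrence, whether the disease is milder".
- The working hypothesis, later in the Discussion, likewise offers fewer infectious cases or, failing that, milder disease.

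Secondary Outcomes lists hospital and ICU admission, pneumonia, oxygen support, gastrointestinal symptoms, days of fever, cough and fatigue, drug use, and vaccine response and side effects. Table 1 ticks a COVID-19 test at V1 and V3; at V2 a result is collected only if a test was done. Exclusion Criteria remove people already positive by PCR or serology.

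**The concern.** Preventing infection and preventing symptoms in infected people are different effects. The abstract conclusion and the hypothesis treat them as alternatives, so the trial should be able to say which one it saw. The primary outcome responds to both and cannot tell them apart, and no listed outcome counts infections regardless of symptoms.

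A symptom effect is plausible on the article's own evidence. The Introduction reports a 48% lower incidence of local respiratory symptoms with this strain in nursing home residents. If the product acted only on symptoms, a positive primary result would still invite the statement that it prevents infection. For health care workers the distinction matters, because someone infected without symptoms is still infected.

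**Working it through.** **1. The plan's own figure.** Sample Size gives 15% affected in the control arm, a 10-point difference (so 5%), α 5%, power 80% and 10% loss. Taking a two-sided test with pooled variance under the null and no continuity correction:

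n = [1.96·√(2·0.10·0.90) + 0.842·√(0.15·0.85 + 0.05·0.95)]² / 0.10² = (0.832 + 0.352)² / 0.01 ≈ 140.1, rounded up to 141 evaluable per arm.

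141 / 0.90 = 156.7, rounded up to 157 per arm. This matches the stated number, and power at 141 per arm is 80%.

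**2. What the primary outcome measures.** In each arm:

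P(symptomatic infection) = P(infected) × P(symptoms given infected).

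The same change in the product can come from either factor.

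**3. Two mechanisms, one primary result.** The documents give neither the infection rate nor the symptomatic share, so the values below are assumed. They are chosen so that the control arm shows the planned 15%.

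| Mechanism | Infected, control / probiotic | Symptomatic share, control / probiotic | Primary outcome | Any infection |
|---|---|---|---|---|
| Symptoms only | 25% / 25% | 60% / 20% | 15% vs 5% | 25% vs 25% |
| Infection only | 25% / 8.3% | 60% / 60% | 15% vs 5% | 25% vs 8.3% |

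Arithmetic: 0.25 × 0.60 = 0.15; 0.25 × 0.20 = 0.05; 0.083 × 0.60 = 0.05.

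Both rows give the planned effect and therefore the same 80% power at 141 per arm. Only the last column separates them, and it is not a listed outcome.

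**4. Range.** The symptoms-only row does not depend on the 60%. With 30% infected in both arms and a share falling from 50% to 16.7%, or 18.75% infected and a share falling from 80% to 26.7%, the primary outcome is again 15% versus 5% with no infection prevented.

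**5. Whether a listed outcome fills the gap.** None does. The secondary outcomes concern severe events, symptoms, medication and vaccination. The scheduled V1 and V3 tests could supply the missing count, subject to the type of test used at V3.

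**The case against.** **The formal aim agrees with the outcome.** This stands. Aim of the Study and the abstract's main outcome both say symptomatic infection. The mismatch is confined to the Discussion's restated aim, the abstract conclusion and the hypothesis. Symptomatic infection is a legitimate primary outcome and need not change.

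**The conclusion is an either/or statement and the outcome responds to either route.** This is true, and it is why the outcome cannot say which route operated. It also stands that the article never plans to report a symptom effect as fewer infections; that is only a reading its wording allows. Nor does the article show that the strain acts on symptoms alone: the same earlier study reports higher seroconversion.

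**A tempting stronger reading concerns the sample size.** Sample Size opens "Given that the current rates of infection among health professionals worldwide are very different", so a reader might infer that 15% is a rate of any infection and that power for symptomatic infection is overstated. The documents do not support this. The 15% is attached to affected individuals, a term left undefined that may mean people with the primary event. The opening clause remarks that rates vary and does not derive 15% from them. Even if 15% did mean any infection, the direction would depend on what is carried over. With an assumed 80% symptomatic share (12% in controls), keeping the two-thirds relative reduction gives 12% versus 4% and 70% power at 141 per arm. Keeping the stated 10-point difference gives 12% versus 2% and 91%. The text shows an undefined term, not a wrong power statement.

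**An outcome added now comes late.** This stands. The intervention part ended in September 2020 and all data collection in September 2021. Table 1 also gives no type for the V3 test. Both limits belong in the fix.

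**Conclusion.** The point holds in a limited form. The article measures symptomatic confirmed infection but in three places promises an answer on infections, and in two of these it treats fewer infections as distinct from milder disease. The primary outcome cannot separate the two, and no listed outcome does.

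The possible size of the misreading is the whole planned effect: under the assumed rates above, 15% versus 5% can arise with no infection prevented. This shows what the outcome can and cannot distinguish; it does not predict what the strain does.

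The point does not invalidate the primary analysis or the sample size, which reproduces exactly. It is a worthwhile correction because it affects what may be concluded from a positive result.

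**What to change.** - **Outcome.** Before unblinding, add as a secondary outcome any PCR- or serology-confirmed infection between V1 and V3, with or without symptoms, in all randomised participants. Label it as added after data collection.
- **Test.** State which test was used at V3. If it was PCR only, say that symptom-free infections that had cleared before V3 may be missed.
- **Wording.** Limit conclusions from the primary outcome to symptomatic infection. In the abstract conclusion, Principal Findings and the working hypothesis, tie fewer infections to the added outcome.
- **Sample Size.** One clarifying sentence at most: which event, over what period, the 15% refers to.

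**Cost.** One extra analysis and some rewording, drawing on tests already scheduled. The outcome comes late and the trial was not sized for it. With 255 recruited against 314 planned, power for the planned 15% versus 5% is already about 76% at 127 per arm with no loss. A null result on the added outcome should therefore not be read as evidence that infection was unaffected.
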